## Abstract

**Background::**

Sedentary behaviour (SB) is associated with adverse health outcomes in the general population. Replacing sedentary time with light intensity physical activity (LPA) has been linked with improvements in all-cause and cardiovascular disease mortality in adults. People with Rheumatoid Arthritis (RA) typically spend long periods of time sedentary, but the health consequences of ‘too much sitting’, and possible benefits of LPA, have not been fully explored in this population. Moreover, little is known regarding the determinants of these behaviours among people living with RA, and such knowledge is required for the development of effective behavioural interventions.

**Aims::**

To examine longitudinal relationships between: 1) objectively-assessed SB/LPA with health outcomes in RA, 2) hypothesised determinants of SB/LPA with objectively-assessed SB/LPA in RA.

**Methods::**

This longitudinal study will secure assessments at baseline (Time 1) and 6-month follow-up (Time 2) from RA patients. At both time points, physical assessments will be undertaken, and questionnaires administered to measure physical (e.g., percentage body fat, disease activity, physical function, pain) and psychological (e.g., depression, anxiety, vitality) health outcomes. Additional questionnaires will be administered to establish hypothesised determinants (i.e., psychosocial, individual differences, and physical environmental). Participants will wear the ActiGraph GT3X accelerometer and activPAL3^μTM^ for 7 days to objectively measure SB and LPA.

**Discussion::**

Findings will elucidate the health correlates of SB in RA, as well as the relevance of interventions targeting reductions in SB by promoting LPA. Results will also assist in identifying intervention targets (i.e., determinants), with the potential to encourage SB change in RA.

## INTRODUCTION

### Rheumatoid Arthritis

Rheumatoid Arthritis (RA) is a chronic autoimmune disease that affects approximately 0.3–1% of people worldwide.^1^ RA is characterised by high-grade local and systemic inflammation, which leads to severe joint pain, stiffness and swelling in synovial joints of the body.^2–4^ People living with RA are exposed to a 50% increase in cardiovascular risk,^5^ with heightened universal inflammation implicated in the common development of cardiovascular disease (CVD) -related morbidity and mortality in this patient group.^6,7–9^ In addition, this elevated inflammation contributes to an increased risk of poor mental health in RA.^10^

### Sedentary Behaviour

Sedentary behaviour (SB) is defined as ‘any waking behaviour characterised by an energy expenditure ≤1.5 metabolic equivalents (METS) while in a sitting, reclining, or lying posture’.^11,12^ It is distinct from physical inactivity, which refers to lack of regular engagement in moderate-to-vigorous intensity physical activity (MVPA [≥3 METS]) in accordance with physical activity recommendations (i.e., 30 minutes × 5 days per week for adults). Examples of common SBs include sitting watching television, reading a book, working at a computer and travelling in a vehicle.^13^ In the general population, SB has been consistently associated with increased inflammation, and it has been proposed that this may represent a mechanism through which SB leads to an increased risk of poor health.^14,15^ For example, prospective studies demonstrate high levels of SB to associate with worsened cardiovascular and cardiometabolic health; both of which are linked to heightened systemic inflammation.^16–25^ In addition, a recent systematic review and dose-response meta-analysis reported that total sitting time and television viewing time were associated with a greater risk of several major chronic disease outcomes, including all-cause, CVD, and cancer mortality, as well as incident diabetes.^26^ Importantly, such adverse health outcomes associated with engagement in SB have been shown to occur, despite the level of MVPA an individual engages in.^27,28^ That is, SB represents an independent risk factor for poor health.^26^

### Sedentary Behaviour and Rheumatoid Arthritis

It has been reported that people living with RA typically spend long periods of time sedentary,^3,29,30^ and recent accelerometry studies suggest people with this condition can spend up to 9 waking hours sedentary per day.^31,32^ On the basis of emerging evidence for the association between SB and inflammation, Fenton and Kitas^29^ hypothesised that high levels of SB in RA may exacerbate already elevated systemic inflammation in these patients, and contribute to the progression of RA outcomes. Akin to this proposition, Fenton et al.^31^ summarised results of non-RA studies, demonstrating the adverse links between SB with inflammation and chronic diseases with an inflammatory component (e.g., CVD, type 2 diabetes), underlining the relevance of these findings for RA. That is, as evidence for the associations between SB, inflammation and poor health continues to accumulate, it is important to evaluate the role of SB as an independent risk factor for disease outcomes in RA – a population experiencing compromised health and at high risk of comorbidity.

Whilst studies to date are yet to determine the role of SB for inflammation in RA, research has begun to examine the implications of SB for broader RA outcomes. Such investigations have employed either device-based, or self-report methods to quantify SB. For example, Khoja et al.^33^ reported positive associations between accelerometer-assessed SB with disease activity, and Greene et al.^34^ and Giles et al.^35^ showed that high levels of self-reported SB was associated with poorer physical function in RA patients. In addition, Prioreschi et al.^3^ used accelerometry to determine SB patterns in people living with RA and found an inverse association between SB and bone mass. More recently, research studies have indicated that higher levels of accelerometer-assessed SB are associated with more pain and fatigue,^36^ and a higher risk of CVD.^37^ Specifically, Fenton et al.^37^ found that total sedentary time was adversely associated with 10-year CVD risk in a sample of RA patients. Interestingly, this study was the first to examine whether the manner in which sedentary time was accumulated held implications for health outcomes in RA. Findings revealed a positive relationship between sedentary time accumulated in bouts ≥20 minutes and 10-year CVD risk.

This finding^37^ is aligned with novel prospective and experimental studies, which indicate that shorter sedentary bouts (i.e., the duration of uninterrupted sedentary periods) and more frequent sedentary breaks (i.e., interruptions in sedentary time)with light physical activity (LPA [1.6 – <3 METS]), are beneficially linked to health outcomes in non-clinical and clinical populations.^20,27,38–43^ For example, regularly breaking up SB with LPA has been associated with better cardiometabolic and cardiovascular health in adults (≥20 years)^20,38^ and older adults,^27^ and has also been linked with a reduced risk of disability among older adults.^41^ A recent systematic review and meta-analysis of experimental and observational studies also revealed that LPA (overall, and sedentary breaks) could play a role in improving adult cardiometabolic health and reducing mortality risk.^44^ In RA, recent studies have reported beneficial associations between daily LPA with CVD risk,^37^ depression and vitality.^45^

Such findings illustrating the potential health benefits of LPA are particularly relevant to people with RA, given the pain and physical dysfunction characteristic of this condition. Indeed, approaches to reduce SB by promoting LPA (‘sedentary breaks’), may be better tolerated than those targeting MVPA, the traditional focus of physical activity behaviour change interventions in this patient group. Moreover, the strong inverse correlation between SB and LPA in studies with RA patients, certainly points to the potential of behavioural interventions which aim to displace SB with LPA among this population.^33,45^

Whilst studies on this topic are beginning to emerge, a number of important limitations mark the extant literature in this field, which should be addressed in future research. First, a heavy reliance on self-report measures to assess SB and physical activity within this patient group brings issues regarding social desirability, errors in participant recall, and a tendency to underestimate levels of SB and overestimate levels of physical activity.^16,46^ Second, whilst several studies have employed accelerometers in an attempt to address the limitations of self-report, sedentariness is often incorrectly defined as activity ≤1 MET^33^ or <1 MET.^47^ As a result, SBs that require between 1–1.5 METS (e.g., sitting whilst watching television or reading) may be misclassified as LPA,^48,49^ meaning the true significance of SB for RA outcomes cannot be accurately determined. Similarly, SB is sometimes defined as ‘lack of engagement in purposeful physical activity’ (i.e., physical inactivity, not meeting MVPA guidelines), which is inconsistent with the definition used by the SB Research Network (i.e., waking behaviour ≤1.5 METS, whilst sitting/reclining/lying),^11,12^ employed almost globally across the SB literature. Finally, the majority of studies that identify associations between SB and health outcomes in RA are cross-sectional, posing a challenge when inferring a causal direction of these associations.^31^ As such, research is required to address these methodological limitations, and generate important knowledge regarding the consequences of SB in RA for inflammatory burden and related RA outcomes. It is also essential that high quality studies investigate the potential benefits of LPA participation for people living with RA, in order to elucidate the potential relevance of interventions that focus on displacing SB with LPA.

### Determinants of Sedentary Behaviour and Light Physical Activity

In order to prevent the potential adverse consequences of SB for health in RA, interventions promoting SB change should target factors that influence this behaviour (i.e., determinants). If interventions are to focus on displacing SB with engagement in LPA, they will also need to consider the determinants of LPA.

#### Psychosocial determinants and individual difference factors

*Self-efficacy.* Social Cognitive Theory (SCT)^50^ regularly serves as the theoretical basis for health behaviour change interventions.^51^ Self-efficacy (i.e., situational-specific confidence), an underlying composite of SCT, has been identified as a consistent predictor of physical activity engagement.^51^ Indeed, it has been well documented that self-efficacy is a significant determinant for the adoption and adherence of physical activity in different populations.^52–54^ Contrastingly, few studies have considered self-efficacy as a determinant for SB change, particularly in the RA population. One study by Huffman and colleagues^47^ indicated that self-efficacy for exercise was negatively and positively associated with SB and physical activity respectively in this patient group. As highlighted above, a criticism of this study is that an incorrect definition of SB as <1 MET was employed.

*Quality of motivation.* Self-Determination Theory (SDT)^55^ proposes that variability in the reasons ‘why’ a person chooses to engage (or not to engage) in a behaviour, holds important implications for levels of engagement. Specifically, SDT suggests that an individual’s motivation may vary in its degree of relative autonomy, with more autonomous reasons for engagement (e.g., fun, enjoyment, personally important) linked to an increased likelihood of adopting and persisting with engagement in a behaviour (e.g., physical activity). In contrast, more controlled reasons for participation (e.g., other people’s approval, feeling guilty) are linked to a lesser chance of sustaining behaviour. The implications of quality of motivation have been demonstrated in a considerable amount of physical activity research with different populations,^56^ including RA.^57^

SDT also postulates that humans have three basic psychological needs; namely, autonomy, competence and social relatedness. Fulfilment of these needs leads to fostering more autonomous motivation towards a behaviour, as well as benefits in mental health (e.g., vitality and well-being).^58^ SDT suggests the social environment is central to the satisfaction of these three basic needs, and holds implications for encouraging behaviour change through promoting more autonomous motivation. Specifically, the provision of autonomy support from an ‘important other’ (e.g., peer, parent, spouse, health professional) is reported to hold positive implications for need satisfaction, quality of motivation and behavioural engagement.^59–62^ Fenton et al.^45^ demonstrated perceptions of autonomy support from an ‘important other’ to be positively associated with LPA, in turn benefiting psychological health (i.e., depression and vitality), in RA patients. However, no studies have examined the role of the basic psychological needs and quality of motivation in this relationship, nor have the determinants of SB accumulation been explored in the RA population through a SDT lens. For example, it is possible that more autonomous motivation for reducing SB (e.g., identification with health benefits) is associated with lower levels of sedentariness.

#### Physical environmental determinants

The physical environment has been identified as a modifiable determinant of SB.^63^ Furthermore, the Systems of SBs framework emphasises the importance of prioritising investigation into physical environmental factors, and their relationship with SB accumulation in different populations. Distinguishing between specific factors within the physical environment (e.g., home, workplace, neighbourhood) has been stressed as important when examining the determinants of SB, in order to ensure interventions can be properly targeted. At present, research studies examining the physical environmental determinants of SB often fail to be domain-specific, which can lead to contradicting evidence.^63^

The Systems of SBs framework also depicts that elements of the physical environment may influence SB engagement in different ways, among different populations. For example, examining the determinants of SB in the workplace might not be as relevant to an older adult population as the home or neighbourhood environment might be.^63^ Indeed, aspects of the home environment, such as the number of televisions and motorised vehicles, have been positively correlated with levels of SB in adults (mean age = 57.5 years).^63^ Furthermore, aesthetic features outside of the home environment (e.g., public parks, trees) have been inversely associated with leisure-time SB in adults (mean age = 52.2 years).^65^

To date, no studies have investigated the physical environmental correlates of SB and LPA in the RA population. This patient group is highly heterogeneous, representing different ages, variability in disease activity, physical function and employment status. This underlines the need to examine physical environmental determinants across multiple domains of SB and LPA engagement (i.e., in the home, workplace and neighbourhood).

### Aims of this research

This study will address the knowledge gaps and limitations of the existing literature, in order to build an evidence base regarding the health-related correlates of SB and LPA, and hypothesised determinants of these behaviours in RA.

The aims of this study are twofold:
To investigate the longitudinal relationships between objectively-assessed SB patterns (i.e., overall sedentary time, sedentary bouts and sedentary breaks) and LPA, with health outcomes in people living with RA. On the basis of evidence establishing an association between SB and inflammation in non-RA cohorts, we hypothesise that SB may contribute to disease outcomes in RA via perpetuating heightened systemic inflammation. As such, our primary health outcomes are: inflammatory biomarkers (e.g., Tumour Necrosis Factor-alpha [TNF-α], Interleukin 6 [IL-6], high-sensitivity C-Reactive Protein [CRP], Erythrocyte Sedimentation Rate [ESR]), which have previously been used as primary endpoints in non-RA studies examining the association between SB, inflammation and health.^14,15^ Secondary health outcomes are: broader disease-related outcomes (e.g., disease activity, CVD risk, pain, fatigue, physical function), indices of psychological wellbeing (e.g., depression, anxiety, vitality, satisfaction with life, positive and negative affect), and quality of life.To examine the longitudinal associations between hypothesised determinants (i.e., psychosocial [e.g., autonomy support], individual differences [e.g., self-efficacy] and physical environmental [e.g., home and neighbour-hood environment]) of SB and LPA (i.e., for: 1) reducing overall SB, 2) regularly breaking up SB and 3) physical activity), with objectively-assessed SB patterns (i.e., overall sedentary time, sedentary bouts and sedentary breaks) and LPA, in people living with RA.

## METHODOLOGY

### Participants and Recruitment

Participants will be recruited from Rheumatology Outpatient Clinics in a hospital in Dudley, England. Inclusion criteria will be: a clinical diagnosis of RA according to the American College of Rheumatology-European League Against Rheumatism (ACR-EULAR) Criteria and aged ≥18 years old. Exclusion criteria will be: wheelchair users and those unable to ambulate independently with the use of an assistive device.

Eligible patients will be approached about the study during Rheumatology Outpatient Clinics. A member of the research team will provide patients with information about study procedures and patients will be given the opportunity to ask the researcher any questions. Willing patients will provide informed consent to participate in the study. This study has been approved by the local National Health Service Research Ethics Committee (West Midlands – Black Country Research Ethics Committee 16/WM/0371).

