### Protocol

This study will adopt a longitudinal design. Participants will be asked to visit the hospital at 2 time points; baseline (Time 1) and 6-month follow-up (Time 2). At each time point, participants will be asked to undertake 2 visits (i.e., visits 1 and 2) separated by a 7-day period. Specific protocols to be followed are described below.

#### Visit 1

Participants will visit the hospital to undertake physical assessments and complete questionnaires. At the end of Visit 1, participants will be fitted with the ActiGraph (GT3X) accelerometer and activPAL3^μTM^ posture sensor to wear for the subsequent 7 days. The researcher will give verbal and written instructions, plus a demonstration, regarding how to wear each device. Participants will also be given the Bouchard Physical Activity Record (BAR)^66^ to complete on 3 of the days during which they wear the GT3X and activPAL3^μTM^.

#### Visit 2

After 7 days, participants will re-visit the hospital to provide a fasted blood sample, and return the GT3X accelerometer, activPAL3^μTM^ posture sensor and BAR to the researcher. During this visit, they will also be asked to complete questionnaires with specific reference to their experiences of pain and fatigue over the previous 7 days.

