### Measures

#### Visit 1

*Participant characteristics.* Information will be recorded pertaining to participants’ age, gender, ethnicity, marital status, education, date of diagnosis, existing chronic conditions (e.g., heart disease, diabetes, depression), current medical treatment, smoking status and living arrangements.

*Anthropometrics.* Taken in duplicate, height, weight and body composition will be measured with participants bare-foot, whilst wearing light and loose-fitting clothing. Height will be measured to the nearest 0.1cm using a stadiometer (SECA, Leicester Height Measure). Weight will be measured to the nearest 0.1kg using the Tanita Body Composition Scales (Tanita BC-418 MA P). Body Mass Index (BMI) will be calculated as weight (kg)/height^2^ (m^2^). Percent body fat and muscle mass will be measured using the Tanita Scales via bioelectrical impedance analysis.

*Resting blood pressure.* Resting blood pressure (systolic and diastolic) will be taken in duplicate with an automatic blood pressure machine (Mindray Accutorr PLUS). The blood pressure cuff will be placed over the brachial artery as standard, after the participant has rested in a supine position for 5 minutes.^36,67^

*Physical function.* Gait speed will be assessed using the 20-Metre Timed Walk Test to provide an objective measure of physical function. Participants’ time to walk from a ‘start line’ to a ‘finish line’, 20 metres apart, will be recorded using a stopwatch. The stopwatch will be started once the participant begins to walk from the ‘start line’, and will be stopped once the participant’s heel has completely crossed the ‘finish line’. Gait speed has been previously used in studies of RA to provide an objective measure of physical function (e.g., walking 15.24 metres).^68^ Research has also shown that slower gait speed is associated with RA outcomes, such as pain, fatigue and joint deformation.^69^ As such, it may also serve as a proxy for other important aspects of RA health, directly related to physical function.

*Questionnaires.* Validated questionnaires will be administered to the participant to assess self-reported RA outcomes and hypothesised determinants of SB and physical activity (see **Table 1**). Questionnaire scores will be calculated according to validated scoring instructions (e.g., mean scores will be calculated for the ‘autonomous motivation for reducing SB’ dimension in the Behavioural Regulation in Exercise Questionnaire-2).

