*Actigraph GT3X.* The GT3X triaxial accelerometer (27g; 3.8cm × 3.7cm × 1.8cm) will be attached to an adjustable elastic belt and worn on the right hip in a vertical position.^70–74^ Participants will be asked to remove the device only for sleeping and water-based activities (e.g., swimming, bathing), and to record all replacement/removal in wear time logbooks provided. The GT3X will record accelerations in 1-second epochs, which will be converted into activity counts. These counts will then be interpreted to determine the frequency, intensity and duration of SB and physical activity.

Data collected by the GT3X will be cleaned and analysed using Actilife Software (version 6). For inclusion in analyses, participants will be required to have worn the GT3X for ≥4 days, for ≥10 hours per day, including a weekend day.^25,75–78^ Non-wear (e.g., 60 minutes of ‘zero counts’) will be defined in accordance with previous research among older adults^75,78^ and people living with RA.^45^ Time spent in SB, LPA and MVPA will be determined using cut-points that have been validated in previous research with adults (e.g., Troiano et al.),^74^ and used in studies investigating SB and physical activity in the general population,^79^ in people with rheumatic diseases^80^ and in osteoarthritis.^81^

*ActivPAL3**^μTM^**.* The activPAL3^μTM^ posture sensor (9g; 2.35cm × 4.3cm × 0.5cm) will be initialised using activPAL3^μTM^ software and attached by the researcher to the front of the right thigh, in a mid-anterior position, with a waterproof, adhesive Tegaderm dressing. Participants will be asked to wear the activPAL3^μTM^ for 24 hours a day to enable assessment of time spent sitting/lying, standing and stepping, as well as sit-to-stand transitions.^82–85^ activPAL3^μTM^ software will be used to download the activPAL3^μTM^ data. Sleep time will be determined using self-reported information from the wear time logbooks and BAR, in conjunction with non-wear periods identified via algorithms applied to GT3X data. Specifically, the GT3X output generated by Actilife details at which time the participant removes (e.g., at bedtime) and replaces (e.g., at waking) the accelerometer throughout the 7-day period. This will be checked against the BAR, which details (over 3 days) when the participant woke up and went to bed.

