### Statistical Analyses

SPSS (version 24) will be used to compute descriptive statistics for all measured variables. These will include information regarding participant characteristics (e.g., gender, mean age, ethnicity), health outcomes (e.g., DAS-28, BMI), determinants (e.g., quality of motivation, self-efficacy), as well as levels of SB and LPA among the RA sample. Missing value analyses will be conducted via multiple imputation^92^ or expectation maximization^93^ methods in SPSS, where missing data does not exceed 5%.

Cross-sectional associations between RA participants’ objectively-assessed SB patterns and LPA, with health outcomes (Aim 1) and proposed determinants (Aim 2) will be examined using correlation and regression analyses. Longitudinal associations from baseline (Time 1) to 6-month follow-up (Time 2) will be analysed using regression models.

*Aim 1.* For cross-sectional analyses, objectively-assessed SB patterns and LPA will be independent variables. Dependent variables will include biomarkers of inflammation, disease activity, CVD risk, pain, fatigue, physical function, depression, anxiety, vitality, satisfaction with life, positive and negative affect, and quality of life. For longitudinal analyses, regression models will examine if changes in objectively-assessed SB patterns significantly predict change in health outcomes from baseline (Time 1) to 6-month follow-up (Time 2). Health outcomes will be examined in separate regression models, but analyses will be adjusted for other factors which may influence these associations, as appropriate (e.g., disease duration, age, gender, current medication, and GT3X and activPAL3^μTM^ wear time).

*Aim 2.* For cross-sectional analyses, the determinants of SB in RA (e.g., autonomy support and self-efficacy for physical activity, reducing SB and breaking up SB) will be independent variables, and objectively-assessed SB patterns and LPA in RA will be dependent variables. For longitudinal analyses, regression models will examine if changes in hypothesised determinants of SB and LPA (e.g., autonomy support for reducing SB) significantly predicts change in objectively-assessed SB patterns and LPA from baseline (Time 1) to 6-month follow-up (Time 2). As above, all analyses will be adjusted for potential confounders (e.g., 7-day pain and fatigue [to consider the possibility of bi-directional relationships], GT3X and activPAL3^μTM^ wear time).

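### Acute infection is neither screened for nor recorded, although it can raise both sedentary time and the primary inflammatory markers in the same measurement week and so create or inflate the Aim 1 association

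*Protocol article*

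**What the plan says.** Under Participants and Recruitment, inclusion requires "a clinical diagnosis of RA according to the American College of Rheumatology-European League Against Rheumatism (ACR-EULAR) Criteria and aged ≥18 years old". The exclusions are "Exclusion criteria will be: wheelchair users and those unable to ambulate independently with the use of an assistive device". Neither list mentions acute infection or other short-term illness.

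Under Aims of this research, "our primary health outcomes are: inflammatory biomarkers", with TNF-α, IL-6, high-sensitivity CRP and ESR named. Under Protocol, the devices are fitted at the end of Visit 1 "to wear for the subsequent 7 days". The blood sample closes that week: "After 7 days, participants will re-visit the hospital to provide a fasted blood sample".

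Under Measures, the Visit 1 health history covers "existing chronic conditions (e.g., heart disease, diabetes, depression), current medical treatment, smoking status and living arrangements". Visit 2 adds the blood sample, DAS-28, and pain and fatigue questionnaires about the past week. Device data count if "participants will be required to have worn the GT3X for ≥4 days, for ≥10 hours per day, including a weekend day", with the same threshold for the activPAL. That rule concerns wear only.

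Under Statistical Analyses, the longitudinal Aim 1 models are change on change: "regression models will examine if changes in objectively-assessed SB patterns significantly predict change in health outcomes". The Aim 1 adjusters are given as examples (disease duration, age, gender, medication, wear time). Pain and fatigue over the 7 days are named as adjusters under Aim 2.

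**The concern.** Exposure and primary outcome share one short window at each time point. A participant who rests through that week with an infection may sit more and, at the end of it, give a blood sample with infection-driven CRP, IL-6 or ESR. Illness is then a common cause of both variables, and it pushes them in the direction the study hypothesises.

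The change models are the more exposed. Differencing removes stable variation between people, but an illness at only one time point stays in both change scores. The longitudinal design is offered as an advance on cross-sectional evidence with uncertain causal direction, so this is where a spurious or inflated association would do most damage. An analysis plan written later cannot adjust for, or run a sensitivity analysis on, a variable that was never collected.

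**Working it through.** **The plan's own figure.** Power Calculation gives n = 125 for high-sensitivity CRP at 80% power and α = 0.05. No effect size or sidedness is stated, so n = 125 cannot be reproduced forwards. Solved backwards with Fisher's z:

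- two-sided: r = tanh[(1.960 + 0.842)/√122] = 0.248
- one-sided: r = tanh[(1.645 + 0.842)/√122] = 0.221

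A correlation of about 0.25 is therefore the yardstick.

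**Inputs.** From the article: n = 125, α = 0.05, taken as two-sided. Assumed, because the article gives no values:

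- f, the share of device weeks affected
- a, the shift in the log marker, in SD
- b, the shift in sedentary time, in SD
- for change scores, within-person correlations of 0.7 (sedentary time) and 0.5 (marker), with illness independent between the two time points

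The true association is set to zero, and all 125 participants are assumed to contribute.

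**Cross-sectional formula.** The illness indicator has variance f(1−f), so

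r = f(1−f)ab / √{[1 + f(1−f)a²][1 + f(1−f)b²]}

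The rejection rate is Φ(atanh(r)√122 − 1.96) + Φ(−atanh(r)√122 − 1.96).

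Example with f = 0.10, a = 2, b = 1: f(1−f) = 0.09, so r = 0.18/√(1.36 × 1.09) = 0.148. The rejection rate is 37.7%.

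| f | a | b | induced r | false-positive rate |
|---|---|---|---|---|
| 5% | 1.5 | 0.5 | 0.034 | 6.6% |
| 5% | 2 | 1 | 0.085 | 15.6% |
| 5% | 2.5 | 1 | 0.102 | 20.4% |
| 10% | 2 | 1 | 0.148 | 37.7% |
| 10% | 2.5 | 1 | 0.172 | 48.6% |

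**Change scores.** The 1s under the root become 1 − 0.5 = 0.5 for the marker and 1 − 0.7 = 0.3 for sedentary time.

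Example with f = 0.05, a = 2, b = 1: f(1−f) = 0.0475, so r = 0.095/√[(0.5 + 0.19)(0.3 + 0.0475)] = 0.194.

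| f | a | b | cross-sectional r, rate | change-score r, rate |
|---|---|---|---|---|
| 2% | 2 | 1 | 0.037, 7.0% | 0.091, 17.3% |
| 5% | 1 | 0.5 | 0.023, 5.7% | 0.057, 9.7% |
| 5% | 2 | 1 | 0.085, 15.6% | 0.194, 58.3% |
| 10% | 2 | 1 | 0.148, 37.7% | 0.311, 94.4% |

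**Check by simulation** (4,000 runs per setting, n = 125). For the four rows above, the cross-sectional rates were 7.8%, 5.8%, 16.2% and 38.4%. The change-score rates were 18.6%, 10.0%, 57.7% and 93.2%. With no affected weeks, both analyses returned 4.4-4.8%.

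**A few individuals.** With shifts of 3 SD (marker) and 1.5 SD (sedentary time), one affected participant in 125 gives a cross-sectional rate of about 6%, and six give about 46%.

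**The case against.** **Other records cover that week.** The activity record logs the dominant activity every 15 minutes on 3 days, with daily pain and fatigue scales. Visit 2 adds 7-day pain and fatigue questionnaires, joint counts and self-rated overall health. Current treatment at Visit 1 might reveal an illness already being treated. A reader might infer that nothing collected could identify a sick week and that the damage is beyond repair, but the article does not support that. An imperfect retrospective screen is possible. It is also non-specific: pain, fatigue and rest are common in RA itself, treatment at Visit 1 misses illness that begins later, and DAS-28 contains ESR, a primary outcome.

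**The adjuster list is open.** Nothing bars 7-day pain and fatigue from the Aim 1 models. That is true, but they are named only under Aim 2 and are weak proxies for infection.

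**The exposure shift may be smaller than assumed.** Sixty minutes of zero counts is the example given for GT3X non-wear, so daytime bed rest may be scored as non-wear or make the week invalid. Wear time is also a named adjuster. This is fair, and it is one reason to show milder shifts.

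**The article is condensed.** A rule for postponing visits could sit in the full protocol, which is not shown. However, the exclusions are written as a complete list and the measures are set out visit by visit.

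**Causal claims are restrained.** Future Research Directions says randomised trials are needed for causality. That softens the consequence of a biased association but does not remove the bias.

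**Conclusion.** The point stands in this form: the listed criteria and measures leave acute infection unhandled as a common cause of exposure and primary outcome, so it can create or inflate the Aim 1 association. It would go too far to conclude that illness does create the association. That depends on the share of weeks affected and the size of the shifts, and the documents give neither.

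With no true association and n = 125, the cross-sectional false-positive rate runs from near nominal (about 7% at 5% affected with mild shifts) to about 38-49% (10% affected, +2 to +2.5 SD in log CRP and +1 SD in sedentary time). For change scores, the scenarios shown give about 10% to 94%. Those figures rest additionally on the assumed within-person correlations. At 5-10% affected with shifts of 2 and 1 SD, the spurious change-score correlation is 0.19-0.31, comparable with the correlation of about 0.25 implied by n = 125.

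**What to change.** - **Record it.** At Visits 1 and 2 of both time points, add one yes/no item on acute infection or other acute illness not due to RA, covering the period from shortly before the device week. The investigators should set the window.
- **Rebook where feasible.** If the answer is yes at Visit 1, move the device week and blood sample together, so that exposure and outcome still refer to the same week.
- **Pre-specify a sensitivity analysis.** Repeat the Aim 1 biomarker models without flagged time points, alongside the analysis that includes them. RA flares stay in. A broad illness definition or a fixed CRP cut-off could remove genuine high-inflammation weeks, so mandatory exclusion is not recommended.

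The cost is one question per visit, occasional rebooking and a slightly smaller sample in the sensitivity analysis. The item addresses this one source of confounding. RA activity that moves both variables remains a separate matter. For weeks measured without the item, the existing records allow only the partial screen described above.
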